### Study endpoints

The primary endpoint measure is to detect differences between MS (active treatment) and FS (control) greater than or equal to 0.10-point change from the baseline questionnaire EQ-5D-5 L® Index, at 1, 6 or 12 months after the surgery.

The secondary endpoint measures are:Differences between intervention groups greater than or equal to 10 point-change from the baseline questionnaire EQ-5D-5 L® utilities such as VAS, SI and HI at 1, 6 or 12 months post-surgery.Early postoperative combined endpoint of four major adverse complications (MAC) at 1 month (safety endpoint), including all-cause mortality, acute myocardial infarction, stroke or transient ischaemic accident, and classification of acute renal failure by Acute Kidney Injury Network (AKIN) greater than or equal to 2. Follow up at 1 year post-surgery.Severe nosocomial infections (pneumonia, early endocarditis, mediastinitis, sepsis).Need for rehospitalisation.Differences between interventions groups greater than or equal to 10 points change from the baseline SATISCORE® questionnaire at 1 and 6 months post-surgery.Postoperative hospital length of stay.Postoperative intensive care unit length of stay.Times for ischaemia and cardiopulmonary bypass (CPB).Mechanical ventilator support after surgery (intubation times).Bleeding in the first 24 h after surgery and transfusion requirements in the first 72 h.New York Heart Association (NYHA) functional class at 1 to 6–12 months.Survival at 12 months.

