**Methods/design:**

The QUALITY-AVR trial is a single-blind, single-centre, independent, and pragmatic randomised clinical trial comparing ministernotomy (“J” shaped upper hemisternotomy toward right 4th intercostal space) to full sternotomy in patients with isolated severe aortic stenosis scheduled for elective aortic valve replacement. One hundred patients will be randomised in a 1:1 computational fashion. Sample size was determined for the primary end point with alpha error of 0.05 and with power of 90% in detecting differences between intervention groups of ≥ 0.10 points in change from baseline quality of life Questionnaire EuroQOL-index (EQ-5D-5 L®), measured at 1, 6 or 12 months. Secondary endpoints are: the differences in change from other baseline EQ-5D-5 L® utilities (visual analogue scale, Health Index and Severity Index), cardiac surgery specific satisfaction questionnaire (SATISCORE®), a combined safety endpoint of four major adverse complications at 1 month (all-cause mortality, acute myocardial infarction, neurologic events and acute renal failure), bleeding through drains within the first 24 h, intubation time, postoperative hospital and intensive care unit length of stay, transfusion needs during the first 72 h and 1-year survival rates. Clinical follow up is scheduled at baseline, 1, 6, and 12 months after randomization. All clinical outcomes are recorded following the *Valve Academic Research Consortium 2 criteria.*

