**Fig. 1 Fig1:**
[figure not shown]
Ministernotomy extended in a J-shape into the right fourth intercostal space. **a** Before sawing. **b** Surgical view after sawing, retraction and cannulation

To date, few clinical trials have been conducted that compare AVR surgery using MS versus FS [7–11]. No significant differences have ever been found, due to inadequate design, lack of statistical power or too small a sample size for the primary endpoint of mortality, even though there have been significant differences in morbidity with MS (lower rates of pain, transfusions, bleeding, mechanical ventilation time, stay in intensive care and hospital, etc.) To detect differences in mortality with sufficient power, over 1100 patients would be needed for each branch of the study. This circumstance caused a spate of retrospective studies analysing propensity scores, and meta-analysis [12–14], which confirmed a reduction in postoperative morbidity, and demonstrated a decrease in early [13–15], and even in late, mortality [13]. But there is an evident bias inherent to retrospective studies. This increased the use of MS worldwide, above all as a result of the spread of TAVIs.

There have been no prospective studies to measure patient quality of life (QOL) and compare the techniques of MS versus FS for AVR. There has only been one retrospective study, with results that are not statistically significant [16]. Two clinical trials have compared TAVI versus FS (the PARTNER [17] and the Core Valve PIVOTAL trials [18]) but they did not analyse MS. QOL has always been relevant to the patient; however, clinicians have not given it enough relevant focus, and it is usually and statistically significant in the first month in favour of TAVI [17, 18], with all data coming from secondary analysis, not primary endpoints.

Patient-reported QOL outcomes were selected to be the primary endpoint because if similar recovery time and QOL to TAVI is demonstrated, MS provides the capacity of implantation of more durable valves; therefore, it would be used in patients at low and intermediate risk, given the unknown long-term durability of TAVI valves after 5 years. To date, however, there has been no specifically designed QOL study. For all of these reasons, we designed this clinical trial to compare the QOL after MS versus FS. Satisfaction with the surgery and morbimortality outcomes will also be measured.

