### Sample size calculation

A review of previous work [28, 29] shows that the standard deviations of the EQ-5D-5 L® index in cardiovascular disease varies between 0.10 and 0.22, while VAS score varies between 8 and 21 depending on the severity. Likewise, in the only (multicentre) study [17] that determines quality of life in aortic stenosis, the standard deviation for high-risk patients scheduled for AVR was 0.17 in patients randomised to FS versus TAVI. For these reasons, on summary of all previous work, we used a standard deviation of 0.15 for the EQ-5D-5 L® index to calculate the sample size.

In QOL studies, it is not only important to ascertain whether there are significant differences, but also to know if these differences are clinically relevant. This is why the concept of the **minimal important difference (MID)** was created, which in previous research among patients with cancer was 0.08 points on the EQ-5D index and 7–11 points on the VAS [29], and in patients with stroke it was 0.10 points on the EQ-index (95% CI 0.08–0.12) [28]. This difference was also 0.06 points (95% CI 0.02–0.10) on the EQ index during the first month in the PARTNER 1 study (transfemoral TAVI versus FS) [17], and 0.12 (95% CI 0.08–0.16) in the CoreValve PIVOTAL trial study [18]. As there was no existing specific calculation of MID for cardiology patients with severe aortic stenosis, we arbitrarily established the interval of 0.10 points on the EQ-5D index (the mean value from previous studies) as the clinically relevant difference to detect. Thus, to detect an MID of at least 0.10 points in the QOL scale EQ-5D-5 L® index, with alpha error of 0.05, beta error of 0.1 and power of 90% for two-tailed contrast of two independent means (SD 0.15), two groups of 48 patients are necessary to provide a minimum of 96 patients. In view of possible losses to follow up, 100 patients will be randomised. If patients drop out or are excluded during the study, additional patients will be recruited until a minimum of 96 patients is achieved, and inclusion of an additional patient will be considered again for each patient not completing the 1-year follow-up assessment.

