### Statistical analysis

Statistical analysis will be performed using IBM SPSS 22.0® for Windows®. First, a descriptive analysis of the study variables will be conducted; the values of quantitative variables will be expressed as mean ± standard deviation (SD) or median (interquartile range) depending on whether distribution of the variable is symmetrical and normal. Qualitative variables will be presented in absolute frequencies and relative frequencies. To analyse the differences between continuous quantitative variables (values of the EQ-5D-5 L® and SATISCORE questionnaires) in the two independent groups (MS vs. FS), Student’s *t* test for two independent samples will be applied in cases where the normality of distribution of the variable data in each of the groups can be accepted, which will be checked using the Kolmogorov-Smirnov test, then histograms and Q-Q plots. In cases where normality cannot be accepted, the corresponding non-parametric Wilcoxon test will be applied. In cases where the normality condition can be accepted, Student’s *t* test for two-tailed samples will be applied to analyse differences between continuous quantitative variables in two associated groups (QOL data) before and after surgery.

We will apply analysis of variance (ANOVA) for repeated measures to analyse the variability, with repeated measurements over time, of certain continuous quantitative determinations of the questionnaires used. The normality of the remainder will be checked using the Shapiro-Wilk test. In the case of statistically significant differences in the contrasted variables measured at different times, the different levels of time will be checked, adjusting the outcomes using the Bonferroni correction.

To analyse if there are differences between qualitative variables, 2 × 2 tables will be prepared and analysed using the Chi-squared (*X*2) statistical test. This analysis will be performed to evaluate the differences in complications and major adverse events of dichotomous variables. The relative risk ratio and the corresponding confidence intervals will be calculated to 95% for the MS versus FS technique as a combined safety endpoint of MAC complications.

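### The primary endpoint can be met at any of three visits with no primary visit or alpha allocation, while the sample size is for a single test at 0.05

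*Protocol article*

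**What the plan says.** Study endpoints sets the primary endpoint as a difference between ministernotomy and full sternotomy of at least 0.10 in change from baseline in the EQ-5D-5L "Index, at 1, 6 or 12 months after the surgery". The abstract uses the same disjunction, "measured at 1, 6 or 12 months", and attaches alpha 0.05 and 90% power to it. Neither place names a primary visit or divides alpha.

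Sample size calculation has one comparison in view. Its target is a true difference of 0.10, and the size is worked out "with alpha error of 0.05, beta error of 0.1 and power of 90% for two-tailed contrast of two independent means". The SD is taken as 0.15, and the result is 48 per group, 96 in all, with 100 to be randomised.

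Statistical analysis describes three routes that could each yield a between-arm result for the questionnaire scores:

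- a t test or Wilcoxon test between arms, with no adjustment stated;
- a repeated-measures ANOVA of certain questionnaire measures, after which, if significant, "the different levels of time will be checked, adjusting the outcomes using the Bonferroni correction";
- growth-curve models giving a between-arm difference, confidence interval and P value at each follow-up time, with no adjustment stated.

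It does not say which of these decides the primary endpoint.

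**The concern.** The word *or* in the endpoint gives the trial three opportunities to succeed, while the sample size describes one. If one significant visit out of three is enough, the visit that carries the claim can be picked after the results are known, and the error rate of the claim depends on an adjustment rule that the article does not clearly state.

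The stakes are not small. The abstract's Discussion and the trial summary both say that a positive result could change the surgical reference standard for aortic stenosis and the control arm of future TAVI trials.

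This is not a detail that an article would normally leave to the analysis plan. The time point belongs to the endpoint definition, and the article states that definition twice, disjunctively both times.

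**Working it through.** **Inputs from the article.** Difference 0.10, SD 0.15, two-sided alpha 0.05, power 90%, 48 per arm (Sample size calculation); visits at 1, 6 and 12 months (Study endpoints).

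**Input assumed.** The correlation *r* between the three visit-wise test statistics is not given, so a range is shown. One anchor is available. All three changes subtract the same baseline score. If the four scores have equal variance and a common correlation ρ, two changes have covariance proportional to 1 − ρ and variance proportional to 2 − 2ρ, so they correlate at exactly 0.5. If follow-up scores correlate more with each other than with baseline, the value is higher. Hence 0.5 to 0.9 is a reasonable working range, and 0 is an outer bound.

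**Step 1: reproduce the plan's figure.** n per arm = 2 × (1.960 + 1.282)² × 0.15² / 0.10² = 47.3, rounded up to 48. The non-centrality at 48 per arm is 0.10 / (0.15 × √(2/48)) = 3.266. Power is 90.4% by the normal approximation and 89.8% by the non-central t. The stated size is therefore correct for one test at 0.05.

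**Step 2: three tests, each read at 0.05.** With independent tests, 1 − 0.95³ = 14.3%. For equal correlation *r*, P(max |Z| > 1.960) by simulation of three normals:

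| r | At least one false positive |
|---|---|
| 0 | 14.3% |
| 0.5 | 12.5% |
| 0.7 | 10.9% |
| 0.8 | 9.8% |
| 0.9 | 8.4% |

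**Step 3: Bonferroni applied to all three between-arm tests.** Alpha per test is 0.05 / 3 = 0.0167, critical value 2.394. The familywise rate is 4.9% at r = 0, 4.5% at 0.5 and 3.0% at 0.9. Power at one specified visit with 48 per arm is 79.4% (non-central t) or 80.8% (normal); with 50 per arm it is 81.3% or 82.6%. Restoring 90% at each visit needs 63 per arm (t) or 61 (normal), before losses.

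**Step 4: power for at least one success under Bonferroni.** With a true 0.10 difference at all three visits, 48 per arm and the normal approximation:

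| r | Power, at least one visit |
|---|---|
| 0.5 | 95% |
| 0.7 | 92% |
| 0.8 | 90% |
| 0.9 | 88% |

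If the 0.10 difference exists at only one visit, the chance of any significant visit is about 82%, close to the per-visit power.

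**The case against.** Four points on the other side deserve weight.

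*The article never says that each visit is tested at 0.05.* True. A reader might infer that it does, and conclude that the false-positive rate simply is 10 to 14%. The documents do not support that as a fact: 0.05 appears as the input to the sample size, and the rates in step 2 hold only if the visit-wise tests are left unadjusted. The top of that range also needs near-zero correlation between visits, which is unlikely when all changes share one baseline.

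*The Bonferroni sentence may be the intended control.* It can be read as a gate followed by adjusted contrasts. But it is limited to certain measures and to levels of time after a significant ANOVA, and it does not mention contrasts between arms. The t or Wilcoxon tests and the growth-curve P values lie outside it as written. Control of the 5% level is unclear rather than plainly absent.

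*A 5% error rate and 90% power are not incompatible.* A reader might infer that the stated alpha and power cannot both be true of this endpoint. That goes too far. Step 4 shows about 88 to 95% power for at least one success under Bonferroni when the effect is present at all three visits. The article does not commit to that pattern, however. Its Background says of quality of life in the TAVI trials that "it is usually and statistically significant in the first month in favour of TAVI", which makes an effect confined to an early visit a case worth planning for.

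*Success might require an observed difference of at least 0.10.* At 48 per arm and SD 0.15 this would hold the three-visit false-positive rate to about 0.3%. But Sample size calculation uses 0.10 as the true difference to detect. Under an observed-difference rule, power at any one visit would be only 50% when the true difference is 0.10, so the 90% could not describe it. This reading is unlikely.

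None of these points supplies a primary visit or an alpha rule.

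**Conclusion.** The point stands in conditional form. The primary endpoint is disjunctive over three visits, no visit or analysis is named as decisive, and the sample size describes one test at 0.05.

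- If the visit-wise tests are unadjusted, the familywise error is about 8 to 12.5% (assumed correlation 0.9 to 0.5; 14.3% at zero).
- If Bonferroni applies, the error is at or below 5%, but power at any one specified visit is about 79% rather than 90%. Power for at least one success is about 88 to 95% only if the 0.10 effect is present at all three visits.

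The figures take the article's difference and SD as given, with 48 evaluable patients per arm. The between-visit correlation and the pattern of effect over time are assumptions. The lack of a decisive visit and analysis does not depend on them, and it should be settled before the data are analysed.

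**What to change.** Preferred: name one primary visit and one primary analysis, and test the other two visits as secondary endpoints in a fixed order, each only if the one before it is significant. The 96 patients, alpha 0.05 and 90% power then stand. The choice of visit is the sponsor's. One month is an option consistent with the first-month TAVI results cited in the Background and Sample size calculation, though those concern a different comparison. Twelve months could also be argued, since replacement of patients is tied to completing the 1-year assessment.

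Alternative: keep all three visits, apply Holm or Bonferroni explicitly to the between-arm comparisons, and restate power as about 79% per visit. Any power quoted for at least one visit should come with the effect pattern and correlation assumed. Keeping 90% at each visit would need 61 to 63 per arm before losses.

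Cost: the edit is short, but it is a mid-trial change, with 75 patients enrolled by November 2017. It needs review by the Institutional Review Board and a registry amendment, both of which the article provides for. It should be made before database lock, with a record that the choice was made without sight of outcome data by arm. The downside is that a difference found only at a non-primary visit could not be called the primary result.

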### Sample size calculation

A review of previous work [28, 29] shows that the standard deviations of the EQ-5D-5 L® index in cardiovascular disease varies between 0.10 and 0.22, while VAS score varies between 8 and 21 depending on the severity. Likewise, in the only (multicentre) study [17] that determines quality of life in aortic stenosis, the standard deviation for high-risk patients scheduled for AVR was 0.17 in patients randomised to FS versus TAVI. For these reasons, on summary of all previous work, we used a standard deviation of 0.15 for the EQ-5D-5 L® index to calculate the sample size.

In QOL studies, it is not only important to ascertain whether there are significant differences, but also to know if these differences are clinically relevant. This is why the concept of the **minimal important difference (MID)** was created, which in previous research among patients with cancer was 0.08 points on the EQ-5D index and 7–11 points on the VAS [29], and in patients with stroke it was 0.10 points on the EQ-index (95% CI 0.08–0.12) [28]. This difference was also 0.06 points (95% CI 0.02–0.10) on the EQ index during the first month in the PARTNER 1 study (transfemoral TAVI versus FS) [17], and 0.12 (95% CI 0.08–0.16) in the CoreValve PIVOTAL trial study [18]. As there was no existing specific calculation of MID for cardiology patients with severe aortic stenosis, we arbitrarily established the interval of 0.10 points on the EQ-5D index (the mean value from previous studies) as the clinically relevant difference to detect. Thus, to detect an MID of at least 0.10 points in the QOL scale EQ-5D-5 L® index, with alpha error of 0.05, beta error of 0.1 and power of 90% for two-tailed contrast of two independent means (SD 0.15), two groups of 48 patients are necessary to provide a minimum of 96 patients. In view of possible losses to follow up, 100 patients will be randomised. If patients drop out or are excluded during the study, additional patients will be recruited until a minimum of 96 patients is achieved, and inclusion of an additional patient will be considered again for each patient not completing the 1-year follow-up assessment.

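### The 90% power is stated for change from baseline in the EQ-5D-5L index, but the SD of 0.15 reads as that of the score itself, so the power for change depends on a baseline to follow-up correlation that the article does not give

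*Protocol article*

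**What the plan says.** All places are in the protocol article.

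- **Study endpoints.** The primary endpoint is a difference between ministernotomy and full sternotomy "greater than or equal to 0.10-point change from the baseline questionnaire EQ-5D-5 L® Index, at 1, 6 or 12 months after the surgery".
- **Abstract, Methods/design.** The power is attached to the same quantity: "power of 90% in detecting differences between intervention groups of ≥ 0.10 points in change from baseline quality of life Questionnaire EuroQOL-index".
- **Sample size calculation.** The section reviews published SDs of the index. In one set of sources the SD "in cardiovascular disease varies between 0.10 and 0.22"; in the aortic stenosis study "the standard deviation for high-risk patients scheduled for AVR was 0.17". It concludes "we used a standard deviation of 0.15 for the EQ-5D-5 L® index to calculate the sample size". The target is "to detect an MID of at least 0.10 points in the QOL scale", tested two-sided at 0.05 with 90% power as a contrast of two independent means. The result is 48 per group, 96 in all, with 100 to be randomised.
- **Statistical analysis.** Questionnaire values are compared between groups by t test, or by Wilcoxon test if not normal. Growth curve models estimate group differences in scores at each follow-up time. The listed model variables are treatment, age, sex, EuroScore, time and treatment by time; the baseline index is not named as a covariate.
- **Limitations of the study.** The sample may be too small if SDs exceed those in earlier research. The change scale is not mentioned.

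No SD of change and no correlation between baseline and follow-up appears anywhere in the article.

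**The concern.** A score and its change from baseline have different SDs unless the correlation between the two readings happens to make them equal. The article claims power for change, but describes the SD behind the calculation as that of the index. If 0.15 is the spread of the score at one time, the 90% for change rests on an assumption about the correlation that is never declared.

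What is at stake is how a null result would be read. A reader would take it as coming from a trial with 90% power to see a 0.10 difference in change. That may be too generous or too modest, and the article gives no means of telling which. The question is separate from whether 0.15 and 0.10 were well chosen; it remains even if both are right.

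**Working it through.** **Inputs.** From Sample size calculation: difference 0.10, SD 0.15, two-sided alpha 0.05, power 90%, 48 per group. The correlation r is not in the documents and is assumed over a range.

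**Step 1: reproduce the plan's figure.** For two independent means,

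n per arm = 2 × (1.960 + 1.282)² × 0.15² / 0.10² = 47.3, rounded up to 48.

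With 48 per arm the power is 90.4% by the normal approximation and 89.8% by the exact (noncentral) t test. The stated figure is right for a variable with SD 0.15.

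**Step 2: move from score to change.** If the score SD is the same at baseline and follow-up,

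SD of change = 0.15 × √(2(1 − r)).

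This equals 0.15 when r = 0.5, is larger below that and smaller above it.

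**Step 3: power for an unadjusted comparison of change** (exact t test, 48 per arm, difference 0.10). The last column is the number per arm needed for 90% power by the normal approximation used in Step 1.

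| r | SD of change | Power | n per arm for 90% |
|---|---|---|---|
| 0 | 0.212 | 63% | 95 |
| 0.2 | 0.190 | 72% | 76 |
| 0.3 | 0.177 | 78% | 67 |
| 0.4 | 0.164 | 84% | 57 |
| 0.5 | 0.150 | 90% | 48 |
| 0.6 | 0.134 | 95% | 38 |
| 0.7 | 0.116 | 99% | 29 |

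The smallest r that gives 90% is 0.50 by the exact t test and 0.49 by the normal approximation.

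**Step 4: how far the threshold depends on the assumptions.**

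- *All 50 per arm analysed:* the threshold falls to 0.48 (0.47 by the normal approximation). Power at r = 0.3 is then 80%, against 78% with 48.
- *Unequal SDs:* if the follow-up SD is k × 0.15, the variance of change is 0.15² × (1 + k² − 2rk), which equals 0.15² when r = k/2. The threshold is 0.40 for k = 0.8 and 0.60 for k = 1.2.
- *Score SD other than 0.15* (normal approximation, 48 per arm): with 0.17 the threshold is 0.60 and with 0.22 it is 0.76. With 0.10, power is 93% even at r = 0.

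**Step 5: comparisons for which 0.15 is the right input.** A t test on follow-up scores alone has 89.8% power whatever r is. A comparison of follow-up scores adjusted for baseline has residual SD 0.15 × √(1 − r²). At r = 0 this is 0.150 and the power 89.8%; at r = 0.5 it is 0.130 and the power 96%. It does not fall below the planned level at any r.

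**The case against.** There are four serious points on the other side.

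*The article never says that 0.15 is the SD of a score at one time.* This is correct. The reading is an inference from the wording: SDs are given for the index, and the 0.17 is for patients scheduled for surgery, although the same sentence also refers to their randomised comparison, which leaves the time point less than certain. The cited sources are not at hand. The inference is strong, but the finding has to be conditional on it.

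*The analysis section compares scores, not only changes.* This also stands. For a comparison of follow-up scores an SD of 0.15 is the right input, and under randomisation the expected difference in change equals the expected difference in follow-up score. But no section names that comparison, or a baseline-adjusted one, as the primary analysis, and the abstract's power statement is explicitly for change. The mismatch is therefore not cured.

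*The threshold of 0.5 is not general.* It needs equal SDs, an unadjusted change comparison and 48 per arm, and it shifts as Step 4 shows.

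*The limitations section already warns about larger SDs.* It does, but the present question arises even when 0.15 is exactly right for the score.

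A reader might infer that the trial is underpowered, or that the sample size is miscalculated. The documents support neither. The figure of 48 reproduces, and above r = 0.5 the plan exceeds 90%. One may think a correlation below 0.5 plausible at 1 month, soon after valve surgery, but the article gives no figure for that reading or for 6 and 12 months.

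**Conclusion.** The concern holds in conditional form. The article states 90% power for a 0.10 difference in change from baseline, but supports it with an SD described as that of the index. If 0.15 is a score SD, equal at both times, and change is compared without adjustment in 48 per arm, the claim needs r of about 0.5 or more. Over r = 0 to 0.7, power runs from about 63% to 99%. Since r is unknown, the direction of any error is unknown too. The fault is an undeclared assumption about the scale of the SD, not an arithmetic slip. It should be corrected, because an unconditional 90% for change is not supported by what the article gives.

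**What to change.** Keep the sample size. In the abstract and in Sample size calculation, state whether 0.15 is the SD of the score or of the change. If it is the SD of the change, saying so settles the point. If it is the SD of the score, do one of the following.

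1. Restate the power for change as conditional on r, over the full range and not only its unfavourable part: about 63% at r = 0, 72% at 0.2, 78% at 0.3, 84% at 0.4, 90% at 0.5, 95% at 0.6 and 99% at 0.7. State the assumptions of equal SDs, an unadjusted comparison and 48 per arm alongside.
2. Tie the power statement to a comparison of follow-up scores adjusted for the baseline EQ-5D-5L index, and name that comparison in Statistical analysis. With SD 0.15 and 48 per arm it gives about 90% or more at any r. The baseline questionnaire is already collected.

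The first option costs only wording, and the stated power becomes conditional. The second also adds the baseline index as a covariate. Neither needs extra patients or extra data.

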### Limitations of the study

Among this study’s limitations, there could be some confusion bias introduced by variables, which will be controlled in the statistical analysis using multivariate linear regression analysis. The absence of masking the surgeon may introduce an unmeasurable bias into the study. The sample size is not designed to detect differences in mortality, although a combined safety endpoint such as this one may help to find differences between groups. The use of general QOL questionnaires such as EQ-5D-5 L means that the outcome does not depend exclusively on the surgical technique employed, but also on other diseases and/or complaints that the patient has previously or that may be acquired in the future, independently of the heart condition. The size of the sample could also be insufficient if the standard deviations are shown to be higher than those presented in previous research.

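### The 0.10 target is called the mean of previous studies, but the four cited values average 0.09; the 90% power is computed correctly and holds only for 0.10 with an SD of 0.15

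*Protocol article*

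**What the plan says.** All the design inputs are in the protocol article, section Sample size calculation.

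- **Target difference.** Four EQ-5D index values are cited: 0.08 (cancer, as a minimal important difference, MID), 0.10 (stroke, as an MID, 95% CI 0.08 to 0.12), and 0.06 and 0.12 (two trials of transcatheter implantation against surgery). After noting that no MID exists for severe aortic stenosis, the article says: "we arbitrarily established the interval of 0.10 points on the EQ-5D index (the mean value from previous studies) as the clinically relevant difference".
- **SD.** A cardiovascular range of 0.10 to 0.22 is cited. For aortic stenosis, from what the article calls the only study, "the standard deviation for high-risk patients scheduled for AVR was 0.17". The article then says: "we used a standard deviation of 0.15 for the EQ-5D-5 L® index to calculate the sample size".
- **Result.** With two-sided alpha 0.05 and 90% power, 48 patients per group (96) are needed, and 100 are to be randomised.

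The Abstract and the Study endpoints section both define the primary outcome as change from baseline in the index, with 0.10 written into the endpoint. The Limitations section warns that the sample size "could also be insufficient if the standard deviations are shown to be higher than those presented in previous research".

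**The concern.** Three things do not sit well together.

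1. The parenthesis in the quoted sentence is a factual statement about the cited values, and they do not give 0.10 at the two decimals in which they are reported. It also pools two kinds of quantity: an MID is a threshold of relevance, whereas a between-group difference seen in a trial is an effect estimate.
2. The SD chosen is smaller than the one cited value from aortic stenosis, and no reason is given beyond a general reference to previous work.
3. The cited SDs are for the index, but the outcome is a change score, whose SD depends on a correlation the article does not state.

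The first two choices both make the stated power more favourable than the neighbouring cited values would. The 0.10 threshold and the 90% are the figures a reader would use to judge whether a null result rules out a worthwhile benefit.

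**Working it through.** **Inputs** (Sample size calculation section): difference 0.10, SD 0.15, two-sided alpha 0.05, power 90%, 48 per arm. Alternative inputs from the same section: SD 0.10 to 0.22 and 0.17; differences 0.08, 0.10, 0.06, 0.12.

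**Step 1: reproduce the plan's figure.** n per arm = 2 × [(1.960 + 1.282) × SD / difference]² = 2 × (3.2415 × 0.15 / 0.10)² = 47.3, rounded up to 48. This matches. Power at 48 per arm is 90.4% by the normal approximation and 89.8% by the noncentral t. The t-test is used for every power below.

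**Step 2: the mean.** (0.08 + 0.10 + 0.06 + 0.12) / 4 = 0.36 / 4 = 0.09. The two MIDs alone: (0.08 + 0.10) / 2 = 0.09. The two trial effects alone: (0.06 + 0.12) / 2 = 0.09. The three values with a confidence interval have a simple mean of 0.093 and an inverse-variance mean of 0.097. None is 0.10 to two decimals except the last, which rounds to it; the article mentions no weighting.

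**Step 3: power at 48 per arm with the article's other cited values.**

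| Difference | SD | Power | N in total for 90% (normal approx.) |
|---|---|---|---|
| 0.10 | 0.15 | 89.8% | 96 |
| 0.09 | 0.15 | 82.9% | 118 |
| 0.10 | 0.17 | 81.4% | 122 |
| 0.09 | 0.17 | 72.8% | 150 |

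Across the cited SD range at 0.10: 99.8% (SD 0.10), 85.8% (midpoint 0.16), 59.6% (SD 0.22). With all 100 randomised patients analysed (50 per arm), the lower three rows of the table become 84.4%, 83.0% and 74.6%.

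**Step 4: change score.** With equal variances at the two visits, SD(change) = SD × √(2(1 − r)). This equals the index SD only when r = 0.5. The article gives no r, so the values below are assumptions, with SD 0.15 at each visit and difference 0.10:

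| r (assumed) | SD of change | Power |
|---|---|---|
| 0.3 | 0.177 | 78.0% |
| 0.5 | 0.150 | 89.8% |
| 0.7 | 0.116 | 98.7% |

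**Step 5: what baseline adjustment would do.** Residual SD = SD × √(1 − r²). At SD 0.17 and difference 0.10, ignoring the one degree of freedom spent on the covariate:

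- r = 0.3: residual SD 0.162, power 84.8%.
- r = 0.5: residual SD 0.147, power 90.9%.
- r = 0.7: residual SD 0.121, power 97.9%.

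These correlations are also assumed.

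**The case against.** The strongest reply is that nothing in the power calculation is wrong. The stated inputs give 48 per arm and 90%, and every lower figure appears only after an input is replaced. That stands. A reader might infer that the trial's true power is 73% to 83% and that the 90% is an error. The document does not support this: those figures are sensitivity results, and the 73% needs both inputs changed at once.

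A reader might also infer that 0.15 is below previous research. It is not: it lies inside the cited 0.10 to 0.22. The 0.17 comes from high-risk patients, while this trial excludes ejection fraction below 40%, redo surgery, emergent surgery and more than moderate obstructive lung disease (Table 2), so a smaller SD is arguable. The article does not make that argument.

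The target is openly called arbitrary, equals the cited stroke MID and lies within the cited values. An average of 0.09 that mixes MIDs with treatment effects has no better claim to be the MID. That too stands, so 0.10 can remain the target; only its stated derivation is wrong.

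The change-score effect can go either way, and the longitudinal models in the Statistical analysis section may do better than a single-visit t-test. This is why the point is put as a condition on the 90%, not as a shortfall.

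The Limitations section does disclose an SD risk, but only for SDs above those in previous research. At SDs already reported there, 0.17 and 0.22, power is 81.4% and 59.6%, so the disclosure is too narrow.

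**Conclusion.** The point holds in a limited form. The statement that 0.10 is the mean of previous studies is incorrect: the cited values average 0.09, and two of the four are not MIDs. The 90% is correctly computed but conditional on three things: a difference of 0.10, an SD of 0.15, and that SD applying to the change score, which with an index SD of 0.15 implies a correlation of about 0.5. Changing one of the first two to a neighbouring cited value costs about 7 to 8 percentage points (89.8% to 82.9% or 81.4%); changing both costs 17 (to 72.8%). These figures assume an unadjusted two-sample t-test at one visit with 48 per arm. The correlation results rest on assumed values and equal variances. The sample size need not change, but the text should not present 90% as unconditional.

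**What to change.** 1. In the Sample size calculation section, either give the mean of the cited values as 0.09 and keep 0.10 as a chosen target, or say that 0.10 is the cited stroke MID. Separate the two MIDs from the two observed treatment effects.
2. State that the SD of 0.15 is assumed for the change score, give the implied correlation (about 0.5 if the index SD is also 0.15), and say why 0.15 was preferred to 0.17.
3. Present the 90% as conditional, with a short range: 83% at 0.09/0.15, 81% at 0.10/0.17, 73% at 0.09/0.17, and 99.8% to 60% across the cited SDs at 0.10.
4. Reword the Limitations sentence to say that SDs within the range already reported would lower power.
5. Keep 96 to 100 patients and add the baseline EQ-5D index as a covariate in the primary comparison. The model covariates listed in the Statistical analysis section (age, sex, EuroScore) do not name it. At 0.10 with SD 0.17 this gives about 91% if the correlation is 0.5, which is an assumption.

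The cost is some rewording, one small table and one added covariate. The stated power reads slightly less favourably, and no extra patients are needed.
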